## **4. SUBJECT SELECTION AND WITHDRAWAL CRITERIA**

### **4.1. Number of Subjects**

Approximately twenty subjects will be enrolled in the study in order to have at least 15 subjects to complete the study. Given the nature of the disease, the sample size for this study was chosen based on feasibility and no specific hypothesis testing is planned.

## 4.2. Inclusion Criteria

Specific information regarding warnings, precautions, contraindications, adverse events, and other pertinent information on the GSK investigational product or other study treatment that may impact subject eligibility is provided in the product label.

Deviations from inclusion criteria are not allowed because they can potentially jeopardize the scientific integrity of the study, regulatory acceptability or subject safety. Therefore, adherence to the criteria as specified in the protocol is essential.

Subjects eligible for enrolment in the study must meet all of the following criteria:

1. Adult male or female at least 18 to 75 years at the time of screening.
2. Subjects must have been on FLOLAN therapy for pulmonary arterial hypertension (PAH) as approved in the product label.
3. Subjects must be on stable doses of their existing FLOLAN treatment for a minimum of 3 months prior to screening;
4. Subjects must be on stable doses of any current PAH treatments other than FLOLAN in the last 30 days;
5. Subjects must walk a distance of at least 150 meters during six-minute walk distance test (6MWD). This test must be completed during the Screening Visit;
6. A female subject is eligible to participate if she is of:
  - Child-bearing potential must have a negative urine pregnancy at screening and baseline and agrees to use one of the contraception methods listed in Section 6.3.5 for an appropriate period of time (as determined by the product label or investigator) prior to the start of dosing to sufficiently minimize the risk of pregnancy at that point. Female subjects must agree to use contraception until the end of follow-up visit.
  - Non-childbearing potential defined as pre-menopausal females with a documented tubal ligation or hysterectomy; or postmenopausal defined as 12 months of spontaneous amenorrhea [in questionable cases a blood sample with simultaneous follicle stimulating hormone (FSH) > 40 MIU/ml and estradiol < 40 pg/ml (<147 pmol/L) is confirmatory].
7. Subjects must be competent to understand the information given in the Institutional Review Board (IRB) or Independent Ethics Committee (IEC) approved informed consent form and must sign the form prior to the initiation of any study procedures.

## 4.3. Exclusion Criteria

Deviations from exclusion criteria are not allowed because they can potentially jeopardize the scientific integrity of the study, regulatory acceptability or subject safety. Therefore, adherence to the criteria as specified in the protocol is essential.

Subjects meeting any of the following criteria must not be enrolled in the study:

1. Subjects who are given FLOLAN for a condition or in a manner that is outside the approved indication.
2. Subjects with congestive heart failure arising from severe left ventricular dysfunction.
3. Subjects, with or without supplemental oxygen, who have a resting arterial oxygen saturation (SaO2) <90% as measured by pulse oximetry at screening.
4. Subjects have been hospitalized as an emergency or visited the emergency room for a condition related to PAH or treatment for PAH in the last 3 months.
5. The subject's clinical condition is such that they are not expected to remain clinically stable for the duration of the study.
6. Female subjects who are pregnant or breastfeeding.
7. Subjects who have demonstrated noncompliance with previous medical regimens.
8. Subjects who have a history of abusing alcohol or illicit drugs within 1 year.
9. Subjects with a diagnosis of active hepatitis (hepatitis B surface antibody and hepatitis C antibody).
10. Subjects who have participated in a clinical study involving another investigational drug or device within four weeks before screening.
11. Subjects who had history malignancies within the past 5 years, with the exception of basal cell carcinoma of the skin or in situ carcinoma of the cervix.
12. Any concurrent condition that would affect the safety of the subject or in the opinion of the investigator it is not in the best interest of the patient to participate in the study.

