| Clinical Labs (Hematology, Chemistry and Urinalysis) | x                   |                                                                     | x                               |                         | x                         | x                 | x                | x                       |                                                                         | x                                                                        | x                                                                              |
| Pregnancy Test (urine)                               | x                   |                                                                     | x                               |                         |                           | x                 | x                | x                                   |                                                                         | x                                                                        | x                                                                                          |
| NT-ProBNP                                            |                     |                                                                     | x                               |                         |                           | x                 | x                |                                     |                                                                         |                                                                          |                                                                                            |
| PGx Sampling                                         |                     |                                                                     | x                               |                         |                           |                   |                  |                                     |                                                                         |                                                                          |                                                                                            |

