### 6.3.4. Clinical Laboratory Tests

The following tests are required at each clinic visit (including early withdrawal, an unscheduled visit and follow-up [if applicable]).

- **Chemistry:** serum alanine aminotransferase (ALT/SGPT), aspartate aminotransferase (AST/SGOT), alkaline phosphatase, gamma glutamyl transferase (GGT), lactate dehydrogenase (LDH), creatine phosphokinase (CPK), total bilirubin, creatinine, sodium, magnesium, potassium, chloride, bicarbonate (CO2), phosphorus-inorganic, calcium, blood urea nitrogen (BUN), uric acid, glucose, total protein, and albumin, thyroid function test (T3, T4 and TSH)
- **Haematology:** haemoglobin, hematocrit, red cell count, red cell indices (mean corpuscular volume [MCV], mean corpuscular haemoglobin [MCH], and mean corpuscular haemoglobin concentration [MCHC]), white blood cell count (total and differential), reticulocyte count, and platelet count.
- Dipstick urinalysis (to measure blood, glucose and protein).
- **Pregnancy:** Urine pregnancy test will be collected at screening, baseline, Week 4 or early withdrawal, and follow-up.

Blood samples for NT-Pro BNP concentration will only be collected at baseline, and at Week 4 or at early withdrawal (if applicable).

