### **8.2. Study Design Considerations**

#### **8.2.1. Sample Size Assumptions**

The sample size for this study is based on feasibility without formal power calculations to justify sample size. Formal hypothesis testing is not planned. The safety and efficacy data will be summarized and precision quantified using 95% confidence intervals.

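### Exclusion 9 glosses active hepatitis with hepatitis B surface antibody, a marker of immunity, and joins it ambiguously by 'and' to hepatitis C antibody, so the printed markers do not match the criterion's intent

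*Protocol*

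**What the plan says.** Protocol Section 4.3, exclusion 9, bars "Subjects with a diagnosis of active hepatitis (hepatitis B surface antibody and hepatitis C antibody", where the parenthesis closes. The protocol defines the hepatitis criterion nowhere else.

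The same section makes the wording binding: "Deviations from exclusion criteria are not allowed because they can potentially jeopardize the scientific integrity of the study". It also has a general safeguard in exclusion 12, which begins "Any concurrent condition that would affect the safety of the subject" and goes on to leave room for the investigator's opinion of the patient's best interest.

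Section 6.3.4 introduces its laboratory list with "The following tests are required at each clinic visit". The list holds chemistry, haematology, dipstick urinalysis and a urine pregnancy test, with NT-Pro BNP at some visits. Table 1 carries the row "Clinical Labs (Hematology, Chemistry and Urinalysis" and separate rows for the pregnancy test, NT-Pro BNP and the pharmacogenetic sample. Neither place lists a hepatitis B or C test.

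On size, Section 4.1 states "Approximately twenty subjects will be enrolled in the study in order to have at least 15 subjects to complete the study", and Section 8.2.1 says "The sample size for this study is based on feasibility without formal power calculations to justify sample size".

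**The concern.** The criterion sets out to exclude active disease but illustrates it with a marker that ordinarily shows the opposite, namely protection by vaccine or a past infection that has resolved. A site that looks for the named result in a subject's records is looking for the wrong one. The connective makes this worse, because 'and' can be read as requiring both antibodies or as listing two separate grounds, and the two readings exclude different people.

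What is at stake is consistent eligibility across centres and, to a small extent, the safety displays. Section 6.3.6.2 item g defines a reportable liver event by multiples of the upper limit of normal (ALT at least 3 times and bilirubin at least 2 times), not by change from baseline. Section 8.3.5.2 displays the percentage of subjects above the reference range. Pre-existing hepatitis could therefore show up in both. In the other direction, a study sized by feasibility has little room to lose suitable subjects to a drafting slip.

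**Working it through.** No sample size, power or alpha formula applies, and the protocol states no figure to reproduce. The check is to run serological profiles through the criterion under each way of reading it.

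**Inputs**
- Markers and connective: Section 4.3, exclusion 9.
- Force of the wording: no deviations from exclusion criteria (Section 4.3) and no waivers (Section 3.1).
- Scheduled tests: Section 6.3.4 and Table 1, with no hepatitis serology.
- Assumption from general serology, not from the protocol: surface antibody marks vaccination or resolved infection and is normally absent in active hepatitis B, while surface antigen marks current infection.

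**Profiles**

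Columns two and three take the parenthesis as the definition. Column four lets the opening words about a diagnosis govern. Column five applies the markers after the proposed correction (surface antigen or hepatitis C antibody).

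| Profile | Both required | Either suffices | Diagnosis governs | Corrected markers |
|---|---|---|---|---|
| 1. Active hepatitis B, surface antibody negative, hepatitis C antibody negative | not captured | not captured | excluded if known | captured |
| 2. Active hepatitis B, surface antibody negative, hepatitis C antibody positive | not captured | captured, only through hepatitis C | excluded if known | captured |
| 3. Immune or vaccinated, hepatitis C antibody negative | not captured | captured | not excluded | not captured |
| 4. Immune or vaccinated, hepatitis C antibody positive | captured | captured | depends on whether hepatitis C is active | captured, through hepatitis C |
| 5. Hepatitis C antibody positive only | not captured | captured | depends on whether hepatitis C is active | captured |

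**What follows**
1. Profile 1 is missed under both readings of 'and'. Profile 2 is picked up only by the hepatitis C marker. The hepatitis B marker therefore never identifies active hepatitis B.
2. The two readings of 'and' fail in different places. Requiring both misses profile 5. Accepting either captures profile 3, who has no disease. No single reading produces both faults.
3. The criterion behaves as intended for hepatitis B only if a site sets the parenthesis aside and relies on the opening words.
4. The corrected markers capture profiles 1 and 2 and leave profile 3 eligible. Profiles 4 and 5 then turn on hepatitis C antibody alone, which may not by itself show that infection is active. The wording change does not settle that point.

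**The case against.** The strongest reply is that the operative words are those about a diagnosis of active hepatitis, and the markers are only a gloss. On that view a subject with diagnosed active hepatitis B is excluded, and a healthy vaccinated subject has no such diagnosis and is not. Exclusion 12 gives the investigator a further ground, and using it is not a deviation. ALT, AST, GGT and bilirubin are measured at screening and baseline. Since no serology is scheduled, surface-antibody status will often be unknown, which limits the effect in practice. The study is descriptive, and its primary measurements are quality of life and dose at discharge.

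Most of this stands, and it rules out three stronger conclusions that a reader might draw:
- That active hepatitis B is admitted. The text supports only that the named markers do not capture it; a known case can still be kept out by the opening words or by exclusion 12.
- That all vaccinated subjects are shut out. A vaccinated subject without hepatitis C antibody meets the markers only under the either-one reading, and only if the site lets the parenthesis override the word diagnosis.
- That recruitment loss can be estimated. The protocol gives no prevalence of immunity in its population, so any count of extra candidates to screen would rest on an outside assumption.

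What the reply does not answer is why the parenthesis is there. It is the protocol's only guide to which result counts, and it points to the wrong one. Exclusion 12 can add an exclusion, but it cannot restore a subject removed under exclusion 9.

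**Conclusion.** The point holds as a drafting error in an eligibility rule, of minor severity. The hepatitis B marker contradicts the criterion's own reference to active disease, the connective can be read in two ways with different results, and nothing else in the protocol corrects either fault.

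The size cannot be put as a number of subjects from the protocol. For scale only, with about 20 enrolled, one subject is 1/20 = 5% of a safety display; that says nothing about how likely such a subject is. No sample size, endpoint or analysis changes.

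The conclusion rests on the serology assumption stated above. It also assumes that at least some sites will take the parenthesis at face value, which the bar on deviations makes reasonable to expect.

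**What to change.** In Section 4.3, exclusion 9, replace hepatitis B surface antibody with hepatitis B surface antigen, and replace 'and' with 'or'. State that the criterion is applied from medical history or available records, so that no test is added to Section 6.3.4 or Table 1.

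The sponsor should also confirm whether hepatitis C antibody is the marker intended for active hepatitis C. A rule on cleared infection should not be written in on the reviewer's initiative, because the protocol does not state one.

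The cost is one line in the next amendment, plus a note to sites about which record to look for. Amendment 1 already made corrections of this kind: it removed conflicting adverse-event wording and restored an omitted laboratory test.

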#### **4.4. Withdrawal Criteria**

Subjects who do not tolerate treatment will be withdrawn from the study. Treatment for subjects withdrawn from the study will be implemented at the Investigator's discretion.

A subject may also be discontinued prior to completion of the study for the following reasons, but not limited to:

- Adverse event (AE) or serious adverse event (SAE) which in the opinion of the investigator requires withdrawal or is thought to be not in the best interests of the subject to continue participation
- Positive pregnancy test
- Consent withdrawn
- Lost to follow-up
- Non compliance to protocol procedures (protocol deviation or violation)
- Termination of study by Sponsor
- Investigator's discretion (The reason will be documented in eCRF.)

## **5. STUDY TREATMENTS**

### **5.1. Investigational Product**

The contents of the label will be in accordance with all applicable regulatory requirements.

GSK will not provide FLOLAN products during the run-in period.

GSK will provide the following vials containing:

- epoprostenol 0.5mg lyophile
- epoprostenol 1.5mg lyophile
- sterile glycine diluent (pH 12)

To prepare the new thermo stable product, patients will reconstitute and dilute one or more vials of epoprostenol lyophile (according to therapeutic need) with two vials of sterile glycine diluent (pH 12), giving 100mL of medication for each day of treatment. This reconstituted infusion is filled into medication cassettes prior to either refrigerated storage or immediate continuous intravenous infusion via a central venous catheter using an ambulatory infusion pump.

Above is a summary of the preparation and descriptions of the investigational product. Specific detailed instructions on dosage, administration, preparation and storage requirements will be provided in the SPM. FLOLAN product label will also be provided.

Under normal conditions of handling and administration, investigational product is not expected to pose significant safety risks to site staff. A Material Safety Data Sheet (MSDS) describing the occupational hazards and recommended handling precautions will be provided to site staff if required by local laws or will otherwise be available from GSK upon request.

Adequate precautions must be taken to avoid direct contact with the investigational product. The occupational hazards and recommended handling procedures are provided in the Material Safety Data Sheet (MSDS).

Investigational product must be stored in a secure area under the appropriate physical conditions for the product. Access to and administration of the investigational product will be limited to the investigator and authorized site staff. Investigational product must be dispensed or administered only to subjects enrolled in the study and in accordance with the protocol.

### **5.2. Treatment Assignment**

All Subjects will be receiving the new thermo stable formulation of FLOLAN during the treatment phase.

### **5.3. Blinding**

This will be a single-arm, open-label study and there will be no blinding.

### **5.4. Product Accountability**

In accordance with local regulatory requirements, the investigator, designated site staff, or head of the medical institution (where applicable) must document the amount of investigational product dispensed and/or administered to study subjects, the amount returned by study subjects, and the amount received from and returned to GSK, when applicable. Product accountability records must be maintained throughout the course of the study.

### **5.5. Treatment Compliance**

Compliance will be assessed by the investigator or designee and recorded in the eCRF.

### **5.6. Concomitant Medications and Non-Drug Therapies**

All concomitant medications taken during the study will be recorded in the CRF with indication, dose information, and dates of administration.

#### **5.6.1. Permitted Medications and Non-Drug Therapies**

Subjects should benefit from the standard of care treatment in PAH, according to local standards and subject conditions. Standard medical treatment administered prior to screening may be maintained throughout the study.

Subjects taking PAH specific medications (see examples below) must have stable PAH therapy for at least 1 month prior to screening and the therapy will need to be maintained throughout the duration of treatment period. No changes to PAH-specific medication are allowed during the treatment period.

Examples of permitted PAH-specific medications, but not limited to:

- vasodilators such as angiotensin-converting enzymes (ACE) inhibitors, calcium channel blockers and nitric oxide
- cyclic guanosine monophosphate (cGMP)-specific phosphodiesterase type 5 (PDE-5) inhibitors such as sildenafil and tadalafil
- Endothelin receptor antagonist (ERA) such as ambrisentan and bosentan

#### **5.6.2. Prohibited Medications and Non-Drug Therapies**

During the study, no other prostanoid therapy or its reformulation will be permitted.

**5.7. Treatment after the End of the Study**

The investigator is responsible for ensuring that consideration has been given to the post-study care of the patient's medical condition whether or not GSK is providing specific post study treatment. The end of the study could be either after the 4-week treatment period or if the subject decided to participate in the optional extension phase, the end of extension phase then will mark the end of the study.

**5.8. Treatment of Study Treatment Overdose**

Please refer to the approved product label.

**6. STUDY ASSESSMENTS AND PROCEDURES**

**Table 1 Time and Events Table**

|                                        |                     | 4-week
Run-in
period                                          | Treatment Phase                 |                         |                           |                   |                  |                                     | Extension Phase                                                         |                                                                          |                                                                                            |
|----------------------------------------|---------------------|---------------------------------------------------------------------|---------------------------------|-------------------------|---------------------------|-------------------|------------------|-------------------------------------|-------------------------------------------------------------------------|--------------------------------------------------------------------------|--------------------------------------------------------------------------------------------|
|                                        | Visit 1             | Phone
call

(occurring
14 days
prior to
baseline) | Visit 2                         | Phone call              | Un-
scheduled
Visit | Early
withdraw | Visit 3          | Follow-
up
Visit  | Phone
call 
at Month
3 (plus
every 6
months) | Clinic
Visit 
at Month
6 (plus
every 6
month) | End of
Extension
Study Visit
or Un-
scheduled
Visit or
Early
withdraw |
| Procedures                             | Screen  | Day-14                                                              | Baseline 
(±7 d) | Day 3, 5, 7
& Week 2 |                           |                   | Week 4
(±7 d) |                                     | Month 3
(±14 d)                                                      | Month 6
(±14 d)                                                       |                                                                                            |
| Written Informed Consent               | x                   |                                                                     |                                 |                         |                           |                   |                  |                                     |                                                                         |                                                                          |                                                                                            |
| Subject Demography                     | x                   |                                                                     |                                 |                         |                           |                   |                  |                                     |                                                                         |                                                                          |                                                                                            |
| Medical/Disease/Therapy
History     | x                   |                                                                     |                                 |                         |                           |                   |                  |                                     |                                                                         |                                                                          |                                                                                            |
| Inclusion/Exclusion
Criteria        | x                   |                                                                     |                                 |                         |                           |                   |                  |                                     |                                                                         |                                                                          |                                                                                            |
| Efficacy Assessments            |                     |                                                                     |                                 |                         |                           |                   |                  |                                     |                                                                         |                                                                          |                                                                                            |
| 6MWD Test                              | x                   |                                                                     | x                               |                         |                           | x                 | x                |                                     |                                                                         |                                                                          |                                                                                            |
| Borg Dyspnoea Index                    | x                   |                                                                     | x                               |                         |                           | x                 | x                |                                     |                                                                         |                                                                          |                                                                                            |
| WHO Functional Class                   | x                   |                                                                     | x                               |                         | x                         | x                 | x                | x                                   |                                                                         | x                                                                        | x                                                                                          |
| QOL and study
Assessment            |                     |                                                                     | x                               |                         |                           | x                 | x                |                                     |                                                                         |                                                                          |                                                                                            |
| Hemodynamic
Parameters  |                     |                                                                     | x                               |                         |                           |                   |                  |                                     |                                                                         |                                                                          |                                                                                            |
| Safety Assessments              |                     |                                                                     |                                 |                         |                           |                   |                  |                                     |                                                                         |                                                                          |                                                                                            |
| Telephone Contact                      |                     | x                                                                   |                                 | x                       |                           |                   |                  |                                     | x                                                                       |                                                                          |                                                                                            |
| Concomitant Medication                 | x                   | x                                                                   | x                               | x                       | x                         | x                 | x                | x                                   | x                                                                       | x                                                                        | x                                                                                          |
| Physical Examination                   | x                   |                                                                     | x                               |                         |                           | x                 | x                | x                                   |                                                                         |                                                                          | x                                                                                          |
| Infusion Site Assessment               | x                   |                                                                     | x                   |                         | x                         | x                 | x                | x                                   |                                                                         | x                                                                        | x                                                                                          |
| Vital Signs                            | x                   |                                                                     | x                   |                         | x                         | x                 | x                | x                                   |                                                                         | x                                                                        | x                                                                                          |

|                                                      |                     | 4-week
Run-in
period                                          | Treatment Phase                 |                         |                           |                   |                  |                                     | Extension Phase                                                         |                                                                          |                                                                                            |
|------------------------------------------------------|---------------------|---------------------------------------------------------------------|---------------------------------|-------------------------|---------------------------|-------------------|------------------|-------------------------------------|-------------------------------------------------------------------------|--------------------------------------------------------------------------|--------------------------------------------------------------------------------------------|
|                                                      | Visit 1             | Phone
call

(occurring
14 days
prior to
baseline) | Visit 2                         | Phone call              | Un-
scheduled
Visit | Early
withdraw | Visit 3          | Follow-
up
Visit  | Phone
call 
at Month
3 (plus
every 6
months) | Clinic
Visit 
at Month
6 (plus
every 6
month) | End of
Extension
Study Visit
or Un-
scheduled
Visit or
Early
withdraw |
| Procedures                                           | Screen  | Day-14                                                              | Baseline 
(±7 d) | Day 3, 5, 7
& Week 2 |                           |                   | Week 4
(±7 d) |                                     | Month 3
(±14 d)                                                      | Month 6
(±14 d)                                                       |                                                                                            |
| Pulse oximetry (oxygen saturation)                   | x                   |                                                                     | x                               |                         | x                         | x                 | x                | x                                   |                                                                         | x                                                                        | x                                                                                          |
| 12-lead ECG                                          | x                   |                                                                     | x                               |                         |                           | x                 | x                |                                     |                                                                         |                                                                          |                                                                                            |
| AE/SAE                                               | x                   | x                                                                   | x                   | x                       | x                         | x                 | x                | x                                   | x                                                                       | x                                                                        | x                                                                                          |
| Lab Assessments                               |                     |                                                                     |                                 |                         |                           |                   |                  |                                     |                                                                         |                                                                          |                                                                                            |
| Clinical Labs (Hematology, Chemistry and Urinalysis) | x                   |                                                                     | x                               |                         | x                         | x                 | x                | x                       |                                                                         | x                                                                        | x                                                                              |
| Pregnancy Test (urine)                               | x                   |                                                                     | x                               |                         |                           | x                 | x                | x                                   |                                                                         | x                                                                        | x                                                                                          |
| NT-ProBNP                                            |                     |                                                                     | x                               |                         |                           | x                 | x                |                                     |                                                                         |                                                                          |                                                                                            |
| PGx Sampling                                         |                     |                                                                     | x                               |                         |                           |                   |                  |                                     |                                                                         |                                                                          |                                                                                            |
